# A single-centre investigator-blinded randomised parallel-group study protocol to investigate the influence of an acclimatisation appointment on children’s behaviour during N_2_O/O_2_ sedation as measured by psychological, behavioural and real-time physiological parameters

**DOI:** 10.1038/s41405-020-0031-y

**Published:** 2020-03-17

**Keywords:** Dental anxiety and phobia, Dental pharmacology

## Abstract

**Aims and objectives:**

To describe a study protocol of a randomised control trial (RCT) assessing the effectiveness, in reducing dental anxiety, of an acclimatising nitrous oxide sedation (N_2_O) session prior to actual dental treatment with N_2_O.

**Materials and methods:**

A single-centre investigator-blinded parallel-group RCT conducted in a postgraduate dental hospital in Dubai, United Arab Emirates (UAE). Anxious children requiring N_2_O (aged 5–15 years) will be randomly assigned to; a study group: children who will have a preparatory N_2_O trial experience or; a control group: children who will only have N_2_O explained to them. Treatment with N_2_O for both groups will start at the second visit. The following outcomes will be recorded: completion of dental treatment, anxiety scores at baseline and after treatment (using the Modified Child Dental Anxiety Scale faces), behaviour of the child (using Frankl Rating Behaviour Scale) and the acquisition of real-time physiological anxiety-related parameters (using E4^®^ electronic wrist devices).

**Results:**

The data will be analysed statistically.

**Discussion:**

There is a paucity of research regarding dental N_2_O acclimatising appointments. This RCT will supplement existing literature.

**Conclusions:**

This RCT will report whether prior acclimatising of a child to N_2_O sedation is effective, or not, in improving dental treatment behaviour.

## Strengths and limitations

No previous study has investigated the effect of an N_2_O/O_2_ sedation acclimatisation visit on children’s anxiety and stress levels as measured by psychological, behavioural and real-time physiological parameters.This study will provide evidence to support the experts’ opinion regarding the implementation of an acclimatisation visit.The study will establish an effective method in the child’s pharmacological behaviour management.However, it may expose the child to an additional N_2_O intervention and increase patient contact time which may affect patient compliance.

## Introduction

Nitrous oxide inhalation sedation (nitrous oxide/oxygen—N_2_O/O_2_ or N_2_O for short) is a mild method of anxiolytic sedation. It is a combination of nitrous oxide and oxygen breathed through a snugly fitting nosepiece, using a special delivery device with robust safety features. This aids the anxious child to feel at ease and allow for dental treatment.^1,2^ It is a known fact that fear and anxiety from dentistry are the most commonly known barriers to receiving actual dental treatment,^3^ with millions of patients reporting that they, if offered some type of anxiolysis/sedation, would be more amenable to accepting dental procedures.^4^

The utilisation of N_2_O or general anaesthesia (GA) is advised by contemporary guidelines to enable the performance of dental treatment in children. This is the case when non-pharmacological behaviour shaping methods fail to lessen children’s anxiety and fear,^2^ and where invasive dental treatment (such as extractions and restorations) are needed particularly in countries that have a very high rate of dental decay such as the United Arab Emirates.^5,6^

The application of N_2_O for dental procedures is essentially reliant on the child’s cooperation, allowance of and maintenance of the N_2_O nasal piece to remain securely in position. If N_2_O is gradually titrated to the appropriate levels for the said child, it provides a mild plane of sedation and anxiolysis to allow for dental treatment.^1,2^

It is suggested that the use of an acclimatisation (familiarisation) visit, defined to be a session in which N_2_O sedation is solely provided, with no or minimal dental intervention, would enhance the acceptability and the efficacy of N_2_O success.^2^ This principle may be contentious. It may increase treatment success and compliance, based on the concepts of graded exposure and cognitive behaviour therapy,^7^ which are behind many well-utilised behaviour shaping modalities. However, it may expose the child patient to further pharmacological intercession and increase patient–dentist contact time, subsequently impacting adversely on patient compliance.

The use of an acclimatising N_2_O session had historically been suggested.^8^ While the sedation guidelines of the Royal Colleges of Surgeons and the Royal College of Anaesthetists in the United Kingdom in 2015 proposed two visits for N_2_O—an assessment session without the use of N_2_O—and a treatment session, they recommended N_2_O to be administered at the first visit in cases of dental emergencies only.^9^ Nevertheless, and most recently, other authorities reverted back to the classical viewpoint. For example, the Scottish Dental Clinical Effectiveness Programme (SDCEP) as recent as 2017 recommended the use of an introductory visit stating “*a brief trial of nitrous oxide/oxygen at the assessment appointment may be helpful for the psychological preparation of some children*”.^2^ Therefore, the aforementioned guidelines have advocated the use of an N_2_O accustoming appointment. Nevertheless, and to our awareness, there are no clinical studies that have investigated the effectiveness of such an acclimatisation visit of N_2_O sedation on the acceptance of the child patients of dental procedures. In addition, no robust, methodically designed and objective randomised control trials exist, to our knowledge, to assess if this preparatory appointment would lead to an enhancement in the patients’ performance and behaviour during the dental procedure.

## The aims of the study

This study is a randomised controlled two-arm trial with a single-centre, single-blinded, parallel-group design. The aims of this clinical research project are to assess the outcome and effect of conducting a short acclimatising preparatory appointment, of 15-min duration using N_2_O sedation, on the objectively assessed behaviour of child dental patients and their perceived and measured levels of anxiety during dental treatment. In addition, this study aims to relate and compare this effect in the study group, with that of a group of children who undergo standard dental treatment without the preparatory accustoming appointment of N_2_O sedation.

### The null hypothesis

The employment of an acclimatising appointment of N_2_O sedation, preceding the instigation of dental treatment will not bring about an enhancement in the child’s behaviour and will not lead to a decrease in anxiety levels throughout dental treatment.

## Materials and methods

The outline of the suggested study is that of a single-centre, single-blinded (to dental surgeon and physiologist investigators), parallel-group randomised controlled two-arm clinical trial, adhering to the guidelines of the CONSORT Group (Schulz et al., 2010)^10^ and to reporting checklist for protocol of a clinical trial based on the SPIRIT guidelines. The overall trial start date (from idea conception) is 01/02/2018, and the proposed end date will be 15/10/2020.

### Primary outcome

The changes in the child’s behaviour and anxiety levels. The primary outcome measures will be assessed byPhysiologically measurable parameters by using a medical grade wearable device (E4^®^ wrist bands—Empatica Inc., [name]—ISO 13485 Cert. No. 9124.EPTC*)*. These parameters areElectrodermal activity (EDA) also known as Galvanic skin response (GSR),Blood volume pulse (BVP),Heart rate (HR),Surface skin temperature.Dental anxiety scores at baseline before the (acclimatisation session) and after treatment (second session) using the Modified Child Dental Anxiety Scale-face version (MCDASf).^11^Children’s behaviour score will be recorded using the Frankl Behaviour Rating Scale (FBRS).^12^

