### Calculation of the study’s sample size

The study is sized to have an 80% power to detect a statistically significant difference in children’s behaviour and anxiety level between the two groups. As there are no previous similar studies, the primary outcome measure is a change in anxiety (a reduction mainly). To our knowledge, no studies had investigated the effect of an acclimatising session of N_2_O on the child’s behaviour to base our sample size calculation on. Our biostatistician used Houpt et al. study in 1996 (effects of nitrous oxide on diazepam sedation of young children) to predict the sample size.^18^ The predicted sample size is 33 participants in each group and to compensate for dropouts a total of 70 participants will be recruited for both groups.

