### Role of the participants and the general public in the study

*What was the research question, the outcome and outcome measures of the study and how were they developed?* A pilot questionnaire to explore the usefulness of an N_2_O acclimatising appointment prior to actual treatment, from the participants’ point of view was carried out in a group of 15 child participants (range: 5–15 years). The outcome of this survey was indecisive with 8 out of 15 children expressing a predilection for commencing treatment without an acclimatising session to N_2_O. This resulted in the formulation of the primary outcome measure of our study on investigating the differences in the participants reported dental anxiety scale in children belonging to the study and control groups.

*What were the preferences and experiences of the participants and their influence in designing the study?* We asked the aforementioned children regarding their feeling in carrying out the completion of the MCDASf (anxiety survey). All the children in this survey mentioned that completing MCDASf was acceptable to them. In addition, we showed and placed the E4 watch on their wrists and asked if they would be happy to wear the watch throughout the treatment. Out of 15 children, 13 were happy with wearing the E4 watch; 2 children found it uncomfortable.

*Involvement of participants in the recruitment to and conduct of the study*. The potential participants will already be patients indicated for N_2_O sedation and are on the DDH sedation list.

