### The study’s statistical analysis

We will conduct deep statistical analysis after consideration of the data’s distribution normality, with the appropriate parametric or non-parametric statistical tests using the statistical software SPSS™ 24.0.0 (SPSS^©^ Inc., USA). The utilisation of standard descriptive statistics and quantitative data will be reported; if normally distributed, means and standard deviations shall be used; and if skewed, medians and interquartile ranges will be reported. The score of dental anxiety will be calculated for each participant and test for normality by using the Shapiro–Wilk test. Categorical data will be tested for independency by using Chi-square or Fisher's exact test when appropriate. The difference in the means between the two groups will be tested using either *t*-test or Mann–Whitney test depending on the normality of the data. The comparison of the means of more than two variables will be tested by using ANOVA or Kruskal–Wallis depending on the normality of the measurements. A *p*-value of <0.05 will be considered significant in all tests.

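### The primary outcome is defined in three inconsistent ways, six measures share primary status with a flat p<0.05, and no rule says which result decides the trial

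*Protocol article*

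**What the plan says.** Four sections of the protocol article bear on this.

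- **Primary outcome.** The concept is "The changes in the child’s behaviour and anxiety levels". The section continues: "The primary outcome measures will be assessed byPhysiologically measurable parameters by using a medical grade wearable device", followed by electrodermal activity (EDA), blood volume pulse (BVP), heart rate (HR) and skin temperature. It then adds "Dental anxiety scores at baseline before the (acclimatisation session) and after treatment (second session" using the MCDASf, and finally "Children’s behaviour score will be recorded using the Frankl Behaviour Rating Scale (FBRS". That makes six measures with no order of importance. A separate Secondary outcomes section follows, so the authors did have a second tier available.
- **Calculation of the study's sample size.** In the singular: "the primary outcome measure is a change in anxiety (a reduction mainly". No instrument is named. The opening sentence of the same section sizes the trial at 80% power for both behaviour and anxiety.
- **Role of the participants and the general public in the study.** The pilot survey is said to have led to the "primary outcome measure of our study on investigating the differences in the participants reported dental anxiety scale" between the groups.
- **The study's statistical analysis.** A p-"value of <0.05 will be considered significant in all tests".

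The null hypothesis section joins two statements: no enhancement in behaviour and no decrease in anxiety.

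**The concern.** A trial needs to fix in advance which result answers its question. Here one section offers six candidates, another offers one construct without an instrument, and a third points to one self-report scale. All tests carry the same threshold.

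Suppose skin temperature differs at p=0.03 and MCDASf does not differ. Under the Primary outcome section this can be presented as a significant primary result. Under the section on the participants' role it is a null result on the primary. The choice could be made after the data are seen. The joint null hypothesis does not settle it: as worded, an effect on either construct makes it false.

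The outcome is also called a change in behaviour. The only Frankl scoring occasion described is during treatment at the second visit (Study flow and layout). The outcome list gives a baseline and a post-treatment time for MCDASf but no times for the Frankl scale.

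**Working it through.** **1. Definitions side by side**

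| Section | What is primary |
|---|---|
| Primary outcome | EDA, BVP, HR, skin temperature, MCDASf, Frankl: six, unranked |
| Sample size, opening sentence | Powered for behaviour and anxiety |
| Sample size, later sentence | A change in anxiety, instrument not named |
| Role of the participants | Difference in the reported dental anxiety scale |

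The six-measure list and the single-measure statements cannot both define the primary outcome.

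**2. The plan's own figure.** The stated size is 33 per group at 80% power. It cannot be reproduced, because the article gives no effect size or SD. Solved backwards for a two-sided 5% test (sidedness is my assumption), the normal approximation gives d = (1.960 + 0.842) × √(2/33) = 0.69. A t-test calculation gives about 0.70.

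**3. Error rate if any one of six counts.** Inputs: six measures (Primary outcome), 0.05 for each (statistical analysis section), one two-sided test per measure (assumption).

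- Independent tests: 1 − 0.95⁶ = 1 − 0.735 = 26.5%.
- Equal positive correlation between the six test statistics (simulation, 400,000 draws): 24.0% at r=0.3, 20.7% at r=0.5, 16.4% at r=0.7, 10.8% at r=0.9.
- Upper bound under any dependence: 6 × 0.05 = 30%.
- Favourable direction only, 0.025 per test: 1 − 0.975⁶ = 1 − 0.859 = 14.1% if independent. Simulated values are about 12% at r=0.3, 10% at r=0.5 and 8% at r=0.7. The comparator for one two-sided 5% test is 2.5%.

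**4. Cost of keeping all six primary.** Bonferroni sets 0.05/6 = 0.0083 per test. With independent tests the overall error is then 4.9%. At the back-solved effect (d about 0.70, not a figure from the article), power per measure with 33 per arm falls from 80% to about 55% by the t-test, or 56% by the normal approximation. About 51 per arm would restore 80% by the normal approximation. A t-test calculation is only a rough guide for the four-level Frankl scale.

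**5. With one primary test at 0.05.** The two-sided error is 5% and the 33 per group is unchanged.

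**The case against.** **The any-one-of-six rule is not in the document.** A reader might infer that the trial has a 26% false-success rate. The text does not support that. It states no rule for combining the results, and sizing the trial for behaviour and anxiety could equally mean that both must succeed. Under an all-must-succeed rule, unadjusted 5% tests do not inflate the error; the cost is power. This stands, so the percentages are conditional on one possible reading.

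**Success has a direction.** The null hypothesis concerns enhancement of behaviour and reduction of anxiety, so a significant result favouring control is not a false success. This stands: 14.1% against 2.5% is the fairer comparison for a false favourable claim. Nor is 26.5% a ceiling, since the bound is 30%.

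**The sample size section does not name MCDASf.** A reader might infer that two sections already make MCDASf the sole primary. Only the section on the participants' role points to the reported scale, and it does so while recounting how the question was developed. Elsewhere the wristband signals are called anxiety-related, so a change in anxiety could include them.

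**Frankl.** A reader might infer that a baseline Frankl score is definitely not collected. That would be reading silence in a condensed article, and the word changes may loosely mean a between-group difference. What stands is that only one scoring occasion is described.

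**An analysis plan may hold a multiplicity rule.** It may, and its absence here is not the complaint. But a rule that adjusted the threshold would contradict the article's flat statement for all tests, and it would not reconcile the differing definitions of the primary outcome.

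**Conclusion.** The concern holds as an inconsistent definition of the primary outcome, combined with a fixed unadjusted threshold and no stated decision rule. The consequence is that the main conclusion is undetermined: the same data could support a positive or a negative report.

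The size of the problem depends on how the results would be combined. If any one of six sufficed, the chance of at least one two-sided false positive runs from 16% to 26.5% over correlations from 0.7 down to zero, and cannot exceed 30%. For favourable errors alone it is 14.1% under independence. These figures assume one test per measure. They show what the wording permits and are not an error rate that the protocol has adopted. The power figures under Bonferroni rest on an effect back-solved from the stated sample size. The inconsistency itself rests on the text alone and needs none of these assumptions.

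**What to change.** Before unblinding:

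1. Name one primary measure and time point, in the same words, in the Primary outcome, sample size and participants' role sections. MCDASf is the measure that the last of these points to: baseline to after treatment at the second visit, compared between arms with adjustment for baseline.
2. Make the Frankl score and the four wristband signals secondary with a Holm adjustment, or label them exploratory.
3. Limit confirmatory p<0.05 to the primary test.
4. Reword the null hypothesis so that the primary null concerns anxiety and behaviour becomes a separate secondary hypothesis. MCDASf does not measure behaviour, so it cannot decide the joint null as now written.
5. Describe the Frankl outcome as a between-group comparison of the second-visit score.

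If behaviour must stay primary, state the multiplicity rule and restate the power, giving the effect size assumed.

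The cost is a protocol amendment; no extra visits, data or participants are needed if one primary is chosen. The Frankl and wristband results lose primary status. That is a real narrowing, because the aims section places behaviour and measured anxiety at the centre of the trial. Keeping several primaries would instead cost power or require more participants.

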### Secondary outcomes

The following clinical outcomes will be obtained and considered as indications of a beneficial effect of the acclimatisation N_2_O session:The successful completion of the required dental procedure as measured by reviewing the clinical notes documents obtained from the electronic dental records system.The children’s and parents’ acceptance of the treatment with or without acclimatisation session as measured by guardian/child quantitative questionnaire (see below Table 1a, b).

**Table 1 Tab1:** Parent’s (a) and children’s (b) dental treatment acceptance questionnaire.

(a) Parent’s dental treatment acceptance questionnaire					
Statements	Response				
	Strongly agree	Agree	No opinion	Disagree	Disagree Strongly
The dentist explained very well why my child needed dental treatment.					
I have no concerns about how the laughing gas sedation works.					
I think the laughing gas sedation is doing a good job at helping my child to cope with the treatment					
My child coped well with having the laughing gas sedation.					
The dental team were kind and helpful during my child’s treatment.					

(b) Children’s dental treatment acceptance Questionnaire			
Questions	Response		
	Positive	Neutral	Negative
What do you think about your experience with laughing gas?			
Are you glad to have your tooth fixed/extracted?			
How did we look after you when you had your treatment?			
How friendly were we when you came to see us?			
How well did the dentist explain everything about treating your tooth?			
Was it ok having your tooth fixed/extracted?			

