**Fig. 3 Fig3:**
[figure not shown]
A child wearing the E4 wrist watch.

Throughout the second visit, the dental treatment for both study and control groups will include administering local anaesthesia and restoration of carious teeth, pulp treatment if needed and/or tooth/teeth extractions. The dental treatment will be carried out by the same paediatric dentist. However, a second paediatric dentist blinded to which group the child belongs to will record the FBRS of children while receiving the treatment under N_2_O sedation.

The MCDASf (see Fig. 2) using the SDCEP endorsed and condensed version of the MCDASf questionnaire,^11^ not including the last two questions on dental sedation and GA, will be used for all anxious children. The MCDASf is a validated tool that had been used to assess dental anxiety.^14–16^

The language of the MCDASf questionnaire will be English or Arabic. The English version was translated into Arabic using the forward and backward translation method. The translation was checked by an independent bilingual expert who resolved concerns and discrepancies. To make sure that the translation was effective, a back-translation to the English language was done by an independent translator who back-translated the questionnaire and discrepancies in the translation version were resolved. The total score range of MCDASf is 6–30. Children with a score ≥19 will be considered to have severe dental anxiety (dental phobia), while those with a score of <19 will be considered to have none to moderate anxiety (Table 2).^7^ The treatment complexity rank score (Table 3) records the medical status classification, based on the patient’s (ASA) classification.^13^

**Table 2 Tab2:** Modified Child Dental Anxiety Scores (MCDAS).

Score	Interpretation
5–10	Minimal anxiety
11–18	Moderate anxiety
≥19	Severe anxiety

**Table 3 Tab3:** Treatment complexity rank score.

Rank	Description	Score
Routine	Polishing, fluoride application, fissure sealants, one-surface Restorations	1
Intermediate	2-surface restorations, extraction of 1 primary tooth, one-quadrant restorative dentistry	2
Complex	Crown preparation, pulp treatment, extraction of multiple primary teeth, multiple-quadrant restorative dentistry, extraction of 1 permanent tooth	3
High complexity	Multiple extractions of permanent teeth, surgical extractions, biopsy. Any treatment considered more complex than above or are multiples of the above	4

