In addition to the MCDASf, physiological anxiety-related changes will be recorded using E4^®^ wrist bands (see Fig. 3). The wrist band will be placed 5 min before the patient comes into the surgery for treatment and will be taken off 5 min after the completion of treatment. This will enable recording physiological parameters continuously before, during and after the dental treatment. E4^**®**^ wrist bands will provide real-time parameters (Fig. 4) such as EDA also known as GSR, BVP, acceleration, HR, and temperature. E4^**®**^ wrist bands are small, simulate wearing a wristwatch, and we do not anticipate any increase in the children’s anxiety as a result of wearing these wrist bands. The E4^**®**^ wrist band was validated^17^ and approved by the United States Food and Drug Administration as a medical device. It is used in a wide range of research settings with configurations for palmar skin conductance measurement or using gelled electrodes secured under the band. Additional evaluation of behaviour (Table 4) will be documented using the numerical FBRS scores (FBRS: 1–4, where 1 is very uncooperative).^12^ Parents and children will be asked to fill in the survey questionnaire after completion of dental treatment visit to assess their perception and approval (or lack of) of dental treatment with or without an accustoming session (Table 1a, b).

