**Fig. 4 Fig4:**
[figure not shown]
The screenshot from the real-time physiological parameter interface obtained from the E4^®^ watch analytical software.

**Table 4 Tab4:** Frankl behaviour rating scale.^12^

	Frankl behavioural rating scale
Rank	Description
1 − −	Definitely negative: Refusal of treatment, forceful crying, fearfulness or any other overt evidence of extreme negativism.
2 −	Negative: Reluctance to accept treatment, uncooperative, some evidence of negative attitude but not pronounced (sullen, withdrawn).
3 +	Positive: Acceptance of treatment; cautious behaviour at times; willingness to comply with the dentist, at times with reservation, but patient follows the dentist’s directions cooperatively.
4 + +	Definitely positive: Good rapport with the dentist, interest in the dental procedures, laughter and enjoyment.

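### Two of the six child acceptance items presuppose a treated tooth and give no answer for a child in whom no tooth was treated

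*Protocol article*

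**What the plan says.** The section Secondary outcomes of the protocol article lists two outcomes as indications of benefit. One is completion: "The successful completion of the required dental procedure as measured by reviewing the clinical notes documents". The other is children's and parents' "acceptance of the treatment with or without acclimatisation session as measured by guardian/child quantitative questionnaire". Table 1b in that section prints the child form, which has six items, each answered positive, neutral or negative. Item 2 reads "Are you glad to have your tooth fixed/extracted" and item 6 reads "Was it ok having your tooth fixed/extracted". Item 1 asks "What do you think about your experience with laughing gas"; items 3, 4 and 5 ask about care, friendliness and explanation.

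On who completes the form and when, Study flow and layout says: "Parents and children will be asked to fill in the survey questionnaire after completion of dental treatment visit". It sets no restriction to children whose treatment succeeded. The same section describes the second visit as local anaesthesia with "restoration of carious teeth, pulp treatment if needed and/or tooth/teeth extractions". The lowest rank of the behaviour scale in Table 4 begins "Definitely negative: Refusal of treatment, forceful crying, fearfulness or any other overt evidence of extreme negativism", so the plan foresees that some children will refuse.

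**The concern.** Items 2 and 6 are the only items that ask how the child felt about having the tooth treated. For a child in whom no tooth was treated, neither has a meaningful answer among the three offered. Such children are likely to have accepted treatment least, and there will be more of them in the control arm if acclimatisation works as hoped.

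Two things can then happen. If the items are blank, or the children are left out, the arms are compared among treated children only, a group selected after randomisation by something that the intervention may change. If the children tick a box, a neutral or negative mark may mean that they disliked the treatment or that it did not take place. The form cannot separate these, and an ambiguous tick from a child of 5 to 15 years cannot be reinterpreted later.

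**Working it through.** **Step 1: the form.** Two of the six items (2 and 6) presuppose a treated tooth. Items 3 and 5 also mention treatment, but ask about the staff and can be answered without a finished procedure. No response for treatment not done is printed.

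**Step 2: available figures.** The protocol article gives no expected completion rate and no expected answer to any item, so there is no figure of its own to reproduce. The only usable number is 33 children per group. Everything below is an illustration with assumed rates.

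**Step 3: treated-only comparison with no true effect on the answers.** Let c0 and c1 be the completion rates in the control and study arms, pa the positive rate among children who would complete in either arm, and pm the positive rate among those who complete only with acclimatisation. Assume that acclimatisation prevents no child from completing and that every non-completer drops out of the two items. The positive share among completers is then:

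- control: pa
- study: (c0 × pa + (c1 − c0) × pm) / c1

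With pa = 0.80 and pm = 0.40:

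| Completion, control v study | Study share among completers | Control share | Difference |
|---|---|---|---|
| 90% v 95% | (0.72 + 0.02)/0.95 = 77.9% | 80.0% | −2.1 points |
| 80% v 90% | (0.64 + 0.04)/0.90 = 75.6% | 80.0% | −4.4 points |
| 70% v 85% | (0.56 + 0.06)/0.85 = 72.9% | 80.0% | −7.1 points |
| 60% v 85% | (0.48 + 0.10)/0.85 = 68.2% | 80.0% | −11.8 points |
| 80% v 80% | 0.64/0.80 = 80.0% | 80.0% | 0 |

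The difference is also 0 whenever pm = pa. If the additional completers answered more positively than the others, its sign would reverse.

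**Step 4: the same children, all randomised.** If every non-completer counts as not positive, the shares are c0 × pa for control and the bracketed sums above for study. At 80% v 90% completion this is 64% v 68% (+4 points); at 60% v 85% it is 48% v 58% (+10 points). The sign differs from the treated-only result because this answers a different question, one that includes completion.

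**Step 5: scale against sampling error.** At 80% v 90% completion, 33 × 0.80 = 26.4 and 33 × 0.90 = 29.7 children are scored. With 80% positive in both arms, the standard error of the difference is √(0.8 × 0.2 × (1/26.4 + 1/29.7)) = 10.7 points, against a shift of 4.4. At 60% v 85%, 19.8 and 28.05 are scored and the standard error is √(0.8 × 0.2 × (1/19.8 + 1/28.05)) = 11.7 points, against a shift of 11.8.

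**The case against.** The strongest reply is that the protocol article nowhere excludes non-completers or allows blank answers, and that scoring rules and the handling of missing items normally sit in the full protocol or analysis plan, which are not shown. This stands against any complaint about an unwritten scoring rule. It does not meet the point about the form, whose wording and response set are printed in full: no later rule can tell what a neutral or negative tick from an untreated child meant.

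A reader might infer that children with failed treatment cannot be scored and that the planned comparison is made among successes only. The text does not support this. A child who refuses can still mark negative. Because the second visit may involve several teeth and procedures, a child who does not complete may still have had a tooth treated. The number of non-completers is therefore an upper bound on the number who cannot answer.

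A reader might also infer that a large benefit is hidden. With assumed completion of 90% v 70% and 80% positive among treated children in both arms, the shares are 72% v 56% of all randomised children and 80% v 80% of the treated. But the 16 points are only (0.90 − 0.70) × 0.80, an assumed completion difference rescaled. They describe a different estimand and do not demonstrate bias. That difference would also appear in the completion outcome, and refusal in the Frankl score, a primary measure.

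Finally, the parent form in Table 1a has items on coping that need no completed procedure, and three of the six child items concern staff for every child, treated or not. Both points stand and limit the weight of the concern.

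**Conclusion.** The point holds in a conditional form. Items 2 and 6 do not fit a child in whom no tooth was treated, although the form is given to all children and completion is an outcome that may differ by arm. A comparison of treated children only follows if such children are left blank or left out; ambiguous data follow if they answer. A shift in the treated-only comparison needs unequal completion, and additional completers who answer differently from the rest. Under the assumed rates it runs from 0 to about −12 points, at most about one standard error with 33 children per arm. None of these rates comes from the protocol article. The weight is minor, since only two items of one secondary questionnaire are affected, but the form has to be changed before it is used.

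**What to change.** - Add a 'treatment not done' response to child items 2 and 6.
- Compare the arms on these items in all randomised children, as positive against not positive. Count 'not done' as not positive where the reason was the child's refusal or non-cooperation, taken from the clinical notes already reviewed for completion.
- Show children not treated for any other reason as a separate category, with their coding fixed in advance.
- Report the comparison among treated children only, labelled as descriptive.
- Report an alternative coding of 'not done' as a sensitivity analysis, because coding it as not positive is open to debate.

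The cost is one response box on two items and a few sentences in the analysis plan, with no new data source. The downside is that the two items then partly repeat the completion outcome, which should be said when they are reported.
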